Net classification improvement will be used as the major statistical analysis for Experimental Aim 2, using ‘standard of care’ screening modality as comparison group. Sensitivity, specificity, positive, and negative predictive values will be calculated, and likelihood ratio will be analysed. C-statistics will be used to compute diagnostic performance of newly validated algorithm. Bootstrapping will be used to generate confidence intervals.

For experimental design Aim 2, sample size calculation is being presented for sensitivity. Assuming a two-sided α of 0.05% and 90% power, and a disease prevalence of 1% consistent with prior newborn CHD screening studies, we based our calculation on methods for diagnostic test evaluation. Specifically, targeting a sensitivity of approximately 90% with a desired confidence interval width of ±10%, at least 19–20 cases of CHD are required. Given the low expected prevalence (1%), this corresponds to a total sample size of approximately 1900–2000 newborns. This approach is consistent with previously published recommendations for validation of diagnostic algorithms in low-prevalence settings.^34^ Accordingly, an independent validation cohort of approximately 1900 consecutively enrolled participants will be used.

Data will be reported as mean ± standard deviation, median (first and third quartile) or frequency (%). All tests were two-sided. A *P*-value <0.05 was considered significant. Standard statistical analysis will be performed using STATA® 17 h Release data analysis software (StataCorp LP, College Station, TX).

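### The Aim 2 sample size states α as 0.05%, almost certainly a slip for 5%, and the 19–20 cases do not follow from 90% ±10% at either level

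*Protocol article*

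**What the plan says.** All of this is in the protocol article under Statistic plan.

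- **Level and power for Aim 2:** "Assuming a two-sided α of 0.05% and 90% power".
- **Precision target:** "targeting a sensitivity of approximately 90% with a desired confidence interval width of ±10" per cent.
- **Cases:** "at least 19–20 cases of CHD are required".
- **Prevalence and total:** "a disease prevalence of 1% consistent with prior newborn CHD screening studies", and "this corresponds to a total sample size of approximately 1900–2000 newborns". The validation cohort is then set at about 1,900.
- **Reporting paragraph, directly after:** "All tests were two-sided" and "A *P*-value <0.05 was considered significant".
- **Aim 1, earlier in the section:** precision of ±2 points for sensitivity and ±4 points for specificity, at the 95% confidence level.

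**The concern.** The section carries two significance levels that differ by a factor of 0.05 / 0.0005 = 100. It gives no multiplicity adjustment or other reason for the stricter one. A reader who tries to reproduce the validation sample size fails with the printed α, and fails again after changing it to 5%. At stake is the one statement that tells readers how precisely the validation phase will estimate sensitivity. As printed, that statement promises ±10 points, which the planned number of cases does not give at 90% sensitivity.

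**Working it through.** **Inputs (Statistic plan).** Sensitivity Se = 0.90, half-width d = 0.10, prevalence 1%, stated result 19–20 cases and 1,900–2,000 newborns.

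**Formula.** Cases = z² × Se × (1 − Se) / d²; total = cases / prevalence.

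**Step 1: what reproduces.** From cases to total: 19 / 0.01 = 1,900 and 20 / 0.01 = 2,000, as stated. Aim 1 also reproduces at the 95% level. Its 600 newborns at 2:1 are 400 diseased and 200 healthy, so:
- sensitivity: 1.96 × √(0.95 × 0.05 / 400) = 0.021
- specificity: 1.96 × √(0.90 × 0.10 / 200) = 0.042

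These match the stated ±2 and ±4 points. The section therefore already works with this formula at α = 0.05.

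**Step 2: α as printed, 0.0005 two-sided (z = 3.481).** 3.481² × 0.09 / 0.01 = 109.04, so 110 cases, or about 11,000 newborns. Other methods do not help: Wilson needs 116 cases, Clopper-Pearson 118, and a one-sided level 98.

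**Step 3: α = 0.05 two-sided (z = 1.960).** 1.960² × 0.09 / 0.01 = 34.57, so 35 cases, or about 3,500 newborns. Wilson needs 37 and Clopper-Pearson 44. A one-sided level needs 25. If the ±10 were a total width (half-width 5 points), the need would be 139.

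**Step 4: what 19–20 cases deliver at Se = 0.90.**

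| Cases | Half-width at α = 0.05 | Half-width at α = 0.0005 |
|---|---|---|
| 19 | 1.960 × √(0.09/19) = 0.135 | 3.481 × √(0.09/19) = 0.240 |
| 20 | 1.960 × √(0.09/20) = 0.131 | 3.481 × √(0.09/20) = 0.233 |

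The Wald interval is rough at this size, since 0.90 + 0.135 exceeds 1. With 18 of 20 cases detected, the 95% Wilson interval runs from 0.699 to 0.972 and the Clopper-Pearson interval from 0.683 to 0.988.

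**Step 5: which inputs do give 19–20.**
- Keeping Se = 0.90 and ±10 points, 19–20 cases correspond to a two-sided α of about 0.14–0.15, which the article names nowhere.
- Keeping α = 0.05 and ±10 points, Se = 0.95 gives 1.960² × 0.0475 / 0.01 = 18.25, so 19 cases and 1,900 newborns.

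**Step 6: the 90% power.** A confidence interval width calculation has no power term. Adding one, (1.960 + 1.282)² × 0.09 / 0.01, gives 95 cases at α = 0.05; with 3.481 in place of 1.960 it gives 205 at α = 0.0005. A one-sample test of 0.90 at two-sided 5% and 90% power needs 42 cases against a null of 0.70 and 137 against 0.80, the range the Introduction gives for pulse oximetry. It comes near the stated number (21 cases) only against a null of 0.60, which the article does not state.

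**The case against.** The strongest reply is that this is a stray percent sign. The Aim 2 calculation concerns precision and specifies no test. The P-value rule is a general reporting convention, and Aim 2 intervals are to be bootstrapped. On this view the slip changes no analysis, no enrolment target and no decision. Most of that stands, and it rules out several stronger readings that a reader might infer:

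- **Two competing decision thresholds for Aim 2, with the analysis 100 times more lenient than the design.** The sample size names no null value and no test, so no acceptance rule is loosened.
- **A loss of power.** A test with 90% power at 0.05 would have 1 − Φ(3.481 − 3.242) = 0.41 at 0.0005, but the plan specifies no such test, so the figure does not describe this study.
- **A cohort that should be about 11,000.** That follows only if 0.05% is meant, and the rest of the section speaks against that.
- **No sensitivity in the article can give 19–20 cases at 0.0005.** At 98%, reported in the Introduction for an earlier paediatric study, the formula gives about 24 cases; at 99%, the upper limit of that study's interval, it gives about 12. So 19–20 lies between them. It is Aim 2's own input of 90% that does not fit.

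What the objection does not remove is Step 3. With the percent sign corrected, the paragraph still gives a case count that its stated inputs do not produce.

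**Conclusion.** The point holds and should be corrected. The printed α is wrong as a design figure and is almost certainly meant as 0.05. The stated 19–20 cases do not follow from 90% ±10 points at α = 0.0005 (110 cases) or at α = 0.05 (35 cases). At the intended 5% level the planned cases give about ±13 points at 90% sensitivity, not ±10.

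This rests on reading ±10% as a half-width and on the normal-approximation formula, which Aim 1 appears to use; the exact and score methods tried need more cases. The totals use the 1% prevalence as stated; the case counts do not depend on it. That 0.95 was the value actually entered is a plausible explanation, because Aim 1 targets sensitivity above 95%, but the article does not say so. A reader might also infer that changing 0.05% to 5% settles the paragraph; Step 3 shows that it does not.

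**What to change.** In the Aim 2 sample size paragraph of the Statistic plan:

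1. Give the level as α = 0.05 (5%), two-sided, with a 95% confidence interval, in line with the reporting rule and Aim 1.
2. Make the precision statement agree with the case count. Either keep 90% sensitivity and say that 19–20 cases give about ±13 points (Wald), or, if 0.95 was the input, state 0.95 with ±10 points and 19 cases.
3. Delete the 90% power, or name the test and the null value to which it applies.

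These are text changes. The cohort of about 1,900 can stay as planned, and no extra enrolment is needed. The cost is a stated precision less favourable than the current ±10 points, unless 0.95 was the input.

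### Aim 2 sample size: 19–20 cases give about ±13 to ±13.5 points around a 90% sensitivity; the stated ±10 points needs 35 cases

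*Protocol article*

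**What the plan says.** All of this is in the protocol article, Statistical considerations, Statistic plan, in the paragraphs on Aim 2.

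- Error rates: "two-sided α of 0.05% and 90% power". Later in the same section: "A *P*-value <0.05 was considered significant".
- Target and result: "targeting a sensitivity of approximately 90% with a desired confidence interval width of ±10%, at least 19–20 cases of CHD are required".
- Step to the total, at 1% prevalence: "this corresponds to a total sample size of approximately 1900–2000 newborns". The cohort is then set at about 1,900 consecutive participants.
- Interval method: "Bootstrapping will be used to generate confidence intervals". This follows sentences on sensitivity, specificity, predictive values, likelihood ratio and the C-statistic. The type of bootstrap is not named.

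Two other places matter. The Aim 1 text in the same section aims for a sensitivity above 95%. The descriptions of the validation phase (Study population and Study procedure) say that newborns are enrolled in high-risk and low-risk strata, without giving the proportions.

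**The concern.** The paragraph gives every input that a precision calculation needs, and the number of cases does not follow from them. This is a stated calculation with a wrong result, not a detail left to another document.

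The number of cases is also the only basis given for the size of the validation cohort. A reader who takes the sentence at face value expects a sensitivity near 90% to be reported with an interval of roughly 80% to 100%. Under the protocol's own assumptions the interval will be clearly wider.

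The sentence also mixes two kinds of calculation. Power needs a null value to test against, and none is given. A confidence-interval width does not use power at all.

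**Working it through.** **Inputs** (all from the Aim 2 paragraph): sensitivity p = 0.90; half-width d = 0.10; prevalence 0.01; stated cases 19–20; cohort about 1,900. The confidence level is taken as 95% (z = 1.96). The printed α of 0.05% appears to be a slip, because the same section uses 0.05 as its significance threshold.

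**1. The plan's own figures.** The step from cases to newborns reproduces: 19 / 0.01 = 1,900 and 20 / 0.01 = 2,000. The step to the number of cases does not:

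n = z² p(1 − p) / d² = 1.96² × 0.90 × 0.10 / 0.10² = 34.6, so 35.

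**2. Other readings of the written inputs.**

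| Reading | Cases |
|---|---|
| 80% two-sided interval | 15 |
| 90% two-sided interval | 25 |
| 95% two-sided, Wald | 35 |
| 95% Wilson | 37 |
| 95% Agresti-Coull | 41 |
| 95% Clopper-Pearson | 44 |
| 90% power term added to the formula, (z for α + z for power)² | 95 |
| α taken literally as 0.05% | 110 |
| ±10% read as a full width of 10 points | 139 |

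None gives 19–20, and 35 is the most lenient of the 95% figures.

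**3. What 19–20 cases deliver at 90% sensitivity** (95% Wald half-width, 1.96 × √(0.09 / n)):

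- n = 19: ±13.5 points
- n = 20: ±13.1 points
- n = 35: ±9.9 points

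Put the other way, ±10 points with 19 cases corresponds to z = 0.10 / √(0.09 / 19) = 1.45, an 85% interval. With 20 cases it is an 86% interval.

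For illustration, exact (Clopper-Pearson) 95% intervals are 66.9% to 98.7% for 17/19 and 68.3% to 98.8% for 18/20.

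**4. Total for the stated precision.** 35 / 0.01 = 3,500 newborns, which is 3,500 / 1,900 = 1.84 times the planned cohort.

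**5. Case count under the 1% assumption.** With 1,900 newborns the number of cases is itself random. Under Binomial(1900, 0.01) the chance of fewer than 19 is 47%.

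**6. Possible origin of the 19.** At p = 0.95 the formula gives 1.96² × 0.95 × 0.05 / 0.10² = 18.2, so 19, which would fit the Aim 1 target. A two-sided test of 0.60 against 0.90 with 90% power gives 20.1. Neither assumption is stated for Aim 2, so the origin stays conjecture.

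**7. Bootstrap (conditional).** Assume a percentile bootstrap of sensitivity with exactly 19 cases. Coverage of the nominal 95% interval is then about 83% at a true sensitivity of 0.90. If all 19 cases are detected, every resample gives 100% and the interval has zero width. The chance of that is 0.90¹⁹ = 13.5%.

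**The case against.** The arithmetic mismatch is not open to much dispute. The best case on the other side limits what follows from it.

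**The cohort may contain more than 1% cases.** The validation phase enrols a high-risk stratum: newborns with a suspicious foetal ultrasound, an abnormal screen or symptoms. Reaching 35 cases in 1,900 needs an overall prevalence of only 35 / 1,900 = 1.84%. This stands. A reader might infer that the study cannot reach ±10 points, and the document does not support that. It shows only that ±10 is not delivered under the assumptions written down. Enrichment does not, however, make 19–20 cases sufficient.

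**The comparison with current screening.** A reader might infer that the miscalculation is what stops the tool being separated from the 70–80% sensitivity quoted for current screening. That does not hold. The major Aim 2 analysis is net classification improvement against standard screening, with both screens done in the same newborns, not a comparison with a literature figure. Even with 35 cases the exact lower limit stays below 80% (73% for 31/35, 77% for 32/35). The 17/19 result used above is an illustration, not a planned outcome.

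**The bootstrap.** A reader might infer that the plan commits to percentile bootstrap intervals for sensitivity. The sentence names no type and directly follows the one on the C-statistic, so it may not cover sensitivity. The type of interval is also commonly left to an analysis plan. The bootstrap point therefore stands only as a conditional remark.

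**Conclusion.** The Aim 2 number of cases is wrong as written. At 90% sensitivity and ±10 points, a 95% interval needs 35 cases by the simplest formula, and 37 (Wilson) or 44 (Clopper-Pearson) by better ones. The plan's 19–20 cases give ±13.5 to ±13.1 points. At the protocol's 1% prevalence, the stated precision would take about 3,500 newborns rather than about 1,900.

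This rests on reading α as 0.05 and ±10% as a half-width; the literal alternatives make the gap larger. Statements about the number of newborns also rest on 1% prevalence in the whole cohort, which the unquantified high-risk stratum may exceed. The finding is that the stated justification does not support the stated precision. It is not that a cohort of 1,900 is unusable.

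**What to change.** **Restate the precision and keep the cohort.** Suggested text: with about 1,900 newborns and 1% prevalence, 19 cases are expected; at a sensitivity of 90% the 95% confidence interval has a half-width of about ±13.5 points (for illustration, the exact interval for 17 of 19 detected is 67% to 99%).

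**Clean up the same sentence.** Delete the 90% power, which has no role in a precision calculation, and correct the α from 0.05% to 0.05.

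**If ±10 points is to be kept**, state the number of cases for the interval method that will be reported: 35 (Wald), 37 (Wilson) or 44 (Clopper-Pearson). At 1% prevalence that is 3,500, 3,700 or 4,400 newborns. If the sponsor expects the high-risk stratum to supply the extra cases, the text should give its share and expected prevalence.

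**Do not simply relabel the assumption as 95% sensitivity.** That fits the assumption to the number afterwards, and a symmetric 95% ± 10 runs from 85% to 105%.

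**Secondary.** Name Wilson or Clopper-Pearson intervals for sensitivity and specificity, and keep the bootstrap for the C-statistic.

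**Cost.** The recommended restatement is wording only, with no extra patients. The price is a less favourable precision statement.

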### Study procedure

#### Patient enrolment

For the derivation phase newborns without SHD will be enrolled at the time of discharge from Ob/Gyn programme and newborns with SHD will be enrolled at the time of cardiovascular examination. For the validation phase consecutive newborns will be enrolled at the time of discharge from Ob/Gyn unit.

*
Graphical abstract
* summarizes the study pipeline.

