
#### Validation phase

Clinical software validation (Aim 2)

After screening of eligible patients written informed consent will be obtained from parents or caregivers.

Clinical screening will be performed as mandated by the Italian law. Pre-ductal (right arm) oxygen saturation and post-ductal (leg) oxygen saturation will be recorded. Physical examination will include femoral arterial pulse detection and face-to-face heart auscultation.

Clinical screening output threshold criteria is summarized in *Table 2*.

**Table 2 ztag103-T2:** Clinical screening output threshold criteria

	Positive screening	Negative screening
**Oxygen saturation**	<95% and/or arm-to-leg difference >5%	>95% and arm to leg difference < 5%
**Femoral arterial pulse**	Absent or reduced	Normal
**Heart auscultation**	Any divergence from normal cardiac auscultation	Normal I/II heart sound, venous hum, physiologic murmur

For this phase we will enrol patients using a block stratification for high SHD risk vs. low (standard) SHD risk status for each newborn.

Heart recordings will be acquired (15 s length) before comprehensive echocardiography by a trained research investigator. Age at recording and echocardiographic evaluation will be planned not before 7 days of post-natal life to allow completion of proper cardio-circulatory transition in the healthy newborns (i.e. ductal closure, pulmonary vascular remodelling, foramen ovale physiologic shunt).

The echocardiography will be performed according to current guidelines by expert paediatric cardiovascular imager blinded to clinical and digital screening results. Preliminary inter- and intra-observer variability between dedicated expert cardiovascular imagers among centres will be performed in small patient subset.

Pertinent anonymized demographics, cardiovascular status, and pertinent research variables will be stored in an encrypted, web-based, research-focused online software.

Digitally anonymized echocardiographic clips will be transferred to the Echocardiography Study Core Lab who will perform the final, formal reading of the exams dichotomizing patient population into normal and abnormal examination. Any potential conflict of interpretation will be solved with consensus and among all Units cardiac imagers.

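### At the plan's 1% prevalence, about 1900 newborns yield 19 CHD cases on average, so the stated minimum of 19–20 is not secured and the ±10-point precision is not reached

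*Protocol article*

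**What the plan says.** The Statistic plan section of the Protocol article sizes Aim 2 on sensitivity, "targeting a sensitivity of approximately 90% with a desired confidence interval width of ±10" percent. It concludes that "at least 19–20 cases of CHD are required". It takes "a disease prevalence of 1% consistent with prior newborn CHD screening studies", converts the case number to roughly 1900–2000 newborns, and ends: "Accordingly, an independent validation cohort of approximately 1900 consecutively enrolled participants will be used".

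The article gives no rule for continuing enrolment until a case minimum is reached, and no range for the number of cases that a fixed cohort may contain.

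Two other places bear on the count. The validation-phase text under Study population defines a high-risk and a low-risk sub-group. The validation-phase text under Study procedure says enrolment is block-stratified by that risk status. Neither gives the proportion of high-risk newborns, and the sample-size paragraph uses a single 1% prevalence.

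**The concern.** A required minimum and an expected count are different things. Dividing the required number by the prevalence returns the cohort size at which that number is the average. About half of such cohorts would fall short. The plan words the number as a minimum and then picks the smallest cohort in its own range.

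Sensitivity is the quantity this cohort is sized for, and fewer missed cases is the main benefit claimed for the tool in the Discussion. A reader would take it that at least 19–20 cases are assured and that they deliver ±10 points. On the printed inputs neither is so.

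**Working it through.** **Inputs (all from Statistic plan).** Prevalence 1%; target sensitivity 90%; half-width 10 points; required cases 19–20; cohort about 1900. The paragraph prints "Assuming a two-sided α of 0.05% and 90% power", but the same section says "A *P*-value <0.05 was considered significant", so I use 5% two-sided (z = 1.96). The 90% power does not enter a precision formula, because no null value or test is stated.

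**Step 1: the plan's conversion to a cohort size.** Cases divided by prevalence: 19/0.01 = 1900 and 20/0.01 = 2000. The division reproduces.

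**Step 2: what 1900 newborns deliver.** If X is the number of cases, X ~ Binomial(N, 0.01). At N = 1900 the mean is 1900 × 0.01 = 19 and the standard deviation is √(1900 × 0.01 × 0.99) = 4.3. The 2.5 and 97.5 percentiles are 11 and 28. Exact tail probabilities:

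| N | P(X ≥ 19) | P(X ≥ 20) |
|---|---|---|
| 1900 | 53% | 44% |
| 2000 | 62% | 53% |

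A 90% chance of at least 19 cases would take 2473 newborns at 1%.

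**Step 3: the case number itself.** Wald formula: n = z² × Se(1 − Se)/d² = 1.96² × 0.9 × 0.1/0.1² = 34.6, so 35 cases. The stated 19–20 does not reproduce. Reading the 5% as one-sided gives 25 cases. Taking the printed α literally gives about 109. A sensitivity of 95% with ±10 gives 18.2, close to 19, but that is not the stated target.

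**Step 4: the precision the cohort supports.** Half-width = 1.96 × √(0.09/k) for k cases at 90% sensitivity:

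| Cases | Half-width (points) |
|---|---|
| 11 | ±17.7 |
| 19 | ±13.5 |
| 20 | ±13.1 |
| 28 | ±11.1 |
| 35 | ±9.9 |

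These are approximations. With 17 of 19 detected, the Wilson interval is 68.6% to 97.1%, a half-width of 14.2 points, so Wald does not overstate the problem.

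**Step 5: dependence on prevalence (N = 1900).** Only the 1% is from the plan; the other prevalences are assumptions.

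| Prevalence | Expected cases | P(X ≥ 19) | P(X ≥ 35) |
|---|---|---|---|
| 1.0% | 19.0 | 53% | 0.1% |
| 1.2% | 22.8 | 82% | 1% |
| 1.5% | 28.5 | 98% | 13% |
| 2.0% | 38.0 | >99.9% | 71% |

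**The case against.** **Dividing by prevalence is normal practice.** It is a common convention in diagnostic studies, and the paragraph hedges with words such as approximately. That stands, and it is why this is a correction of a statement and not a broken design. But the paragraph words the case number as a minimum, not as an expectation.

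**The real cohort may hold more cases.** High-risk newborns have, by definition, a suspicious foetal scan, an abnormal screen or signs, and the study's target condition (structural heart disease) is wider than the congenital disease to which the Introduction's one-in-a-hundred figure refers. Both could lift the case count above 1%. This also stands. A reader might infer that the trial will miss its minimum half the time. The documents do not support that: the 53% describes the sizing paragraph at its printed prevalence, and with no split given the odds for the actual cohort cannot be computed. Nor can the plan take credit for an enrichment that its calculation did not use.

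**Losses.** A reader might also infer that losses make the shortfall worse, because "For the validation phase consecutive newborns will be enrolled at the time of discharge from Ob/Gyn unit" while "Age at recording and echocardiographic evaluation will be planned not before 7 days of post-natal life". The article gives no loss rate. It excludes newborns in whom a diagnostic echocardiogram cannot be acquired, so the 1900 may already mean verified newborns. The full protocol, which is not shown, may contain an allowance. No figure for losses belongs in this point.

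**The case requirement matters more than chance.** A reader might blame random variation in the case count for missing ±10 points. Step 4 shows otherwise: even 28 cases, the favourable end of the range, give ±11.1. Securing 19–20 cases would not deliver the stated precision.

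**Conclusion.** The point holds, limited to what the sample-size paragraph states. On its own 1% prevalence, about 1900 newborns give 19 cases on average (95% range 11 to 28), with a 53% chance of 19 or more and 44% of 20 or more. The number called a minimum is therefore only an expectation. The ±10 points around 90% sensitivity is not reached anywhere in that range; about ±13.5 is what 19 cases support, and ±10 takes about 35.

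This rests on three assumptions: 1% prevalence in the whole cohort, a 5% two-sided level, and 1900 newborns with both a usable recording and an echocardiogram. The first is the weak one, because of the high-risk block. Enrichment could remove the shortfall against 19 cases. At an assumed 1.5%, however, the chance of the 35 cases needed for ±10 is still only 13%. The correction is worth making because it is cheap and the figure is relied on.

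**What to change.** In the Aim 2 sample-size paragraph:

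1. Replace the minimum of 19–20 cases with a statement that, at 1% prevalence, 1900 newborns with an evaluable recording and echocardiogram are expected to yield about 19 cases (95% range 11 to 28).
2. Replace the ±10 with the approximate half-widths at 90% sensitivity: ±13.5 points at 19 cases, ±17.7 at 11 and ±11.1 at 28. Note that ±10 would need about 35 cases.
3. State that these figures assume 1% prevalence, and reconcile that with the high-risk/low-risk block enrolment by giving the intended split or by saying how it affects the expected count.

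**Cost.** This is a change of wording and needs no added patients. The published precision becomes less favourable. If 1900 is defined as evaluable newborns and some recordings prove unusable, enrolment would have to run somewhat higher; the article gives no basis for saying by how much.
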